## Abstract

**Introduction:**

RECONCILE (ClinicalTrials.gov:NCT04340245) will identify molecular and radiomic markers associated with clinical progression and radiological progression events in a cohort of localised, newly diagnosed Gleason 3 + 4 tumours. Molecular markers will be correlated against standard of care MRI-targeted histology and oncological outcomes.

**Methods:**

RECONCILE is an ethics approved (20/LO/0366) single centre, prospective, longitudinal, observational cohort study of recently diagnosed (within 12 months), organ-confined Gleason 3 + 4 cancers (MCCL ≤10mm) currently under active surveillance. 60 treatment-naïve participants with a concordant MRI lesion (Likert score 4 or 5) and PSA ≤ 15 ng/ml will be recruited.

Blood, urine and targeted prostate tissue cores will be subject to next generation sequencing at baseline and one year in all participants. Semen will be collected from a specified sub-population. Baseline and interval MR images will be extracted from standard of care prostate MRI ahead of radiomic analysis. Data extracted from radiological and biological samples will be used to derive the association of molecular change and radiological progression, the primary outcome of the study.

To compensate for spatial intratumoral heterogeneity and inherent sampling bias, a molecular index will be derived for each participant using the molecular profile of tumour tissue at both baseline (MolBL) and one year (MolFU). We will extract a ΔMolBL:MolFU score for each participant. Molecular progression will be defined as a MolBL:MolFU score >95% CI of the combined ΔMolBL scores. Radiological progression is defined as a PRECISE score of 4 or 5. The study is powered to detect an association with a statistical power of 80%.

**Results:**

Recruitment began in July 2020 (n = 62). To date, 37 participants have donated tissue for analysis.

**Conclusion:**

We have designed and implemented a prospective, longitudinal study to evaluate the underlying molecular landscape of intermediate risk, MR-visible prostate tumours. Recruitment is ongoing.

## 1. Introduction

Prostate cancer is the most common cancer in men and second most common cause of male cancer-related death in the UK [1]. There is discrepancy between its high incidence and low mortality rate, and so far, we have been unable to accurately identify cancers which will benefit from early treatment, and those which can be safely surveyed. Prospective randomised controlled trials have demonstrated no impact on disease specific survival when curative intervention is delayed using active surveillance and have called into question the clinical significance of Gleason 3 + 4 disease, which forms the bulk of incidentally detected prostate cancers [2,3].

The RECONCILE study will follow a cohort of newly diagnosed multiparametric magnetic resonance imaging (MRI) visible Gleason 3 + 4 prostate tumours over a one-year period of standard of care active surveillance. The cohort will be deeply characterised using radiomic, tissue and fluidic analysis at baseline and one year. Molecular and radiomic markers associated with radiological and clinical progression events will be extracted from research samples and used to derive the association of molecular change and radiological change (in particular radiological progression), the primary outcome of the study. Markers will be correlated against standard of care MRI-targeted histology and oncological outcomes to further risk stratify this cohort of intermediate risk disease at the time of baseline diagnosis.

### 1.1 Background and rationale

Long term follow-up of localised prostate cancer cohorts suggests limited benefit of radical intervention. Twenty-nine year follow up within the SPCG-4 trial suggests a low survival benefit of an additional 2.3 years (1 in every 8.4 treated) in those randomised to radical prostatectomy vs watchful waiting [2]. The absolute benefit associated with radical prostatectomy increased by a factor of more than 2 between 10 and 23 years of follow-up for both overall, and disease-specific mortality. The time taken to observe a substantial benefit from treatment suggests the need to carefully select those who may benefit from early intervention and to consider deferring curative treatment in those with lower-risk disease. Subgroup analysis also suggested the risk of death associated with Gleason 3 + 4 disease to be similar that of low-grade Gleason 6 tumours, calling into question the benefit of early, radical intervention in this cohort [2].

The UK ProtecT trial similarly showed encouraging results for men with localised cancers wishing to pursue surveillance in the first instance [3]. The study randomised patients with prostate specific antigen (PSA) screen detected cancers to surgery, radiotherapy, or active surveillance and found no difference in survival between radical treatment and monitoring groups at 10 years. Transition to radical treatment was permitted in the monitoring arm in case of clinical and biological progression Surveillance was therefore considered a safe option for men with localised disease even before the era of MRI-led diagnosis [4].

Multiparametric MRI now forms the cornerstone of localised prostate cancer diagnosis and is recommended prior to diagnostic biopsy in several clinical guidelines [4–6]. Aside from offering a target for biopsy and treatment planning, mpMRI provides the unprecedented opportunity to track prostate cancer over time. Prior to the MRI era, surveillance depended heavily upon systematic, non-targeted biopsy. MRI features together with targeted histological data have significantly improved our understanding of individual tumour characteristics and for the first time allow us to prospectively study tumour dynamics.

Novel biomarkers (radiomic, tissue-based and fluidic) may further refine risk stratification and identify tumours where surveillance may be favoured. Genomic, transcriptomic, epigenomic and methylomic analysis has identified vast underlying molecular heterogeneity within prostate cancer foci and suggests that this is unlikely to be a disease where there is a single actionable target [7,8]. Numerous molecular aberrations have, however, been found to be prognostic for disease recurrence, and may represent useful predictors of disease risk [8]. To our knowledge, a longitudinal assessment of molecular changes within a single prostate cancer focus, such as the planned analyses within RECONCILE, has never been performed and remains poorly understood. It is however, known that the molecular landscape of early prostate cancer differs from late stage, metastatic castrate resistant prostate cancer [8]. A longitudinal assessment of prostate cancer molecular heterogeneity over time may therefore help determine the optimal “time to treat” for those who pursue surveillance. Beyond genomic analysis, the immunological environment of a localised prostate tumour is completely unexplored. The dynamics of a related immune response will be explored longitudinally within RECONCILE to further understand this process and its contribution to prostate cancer aetiology and progression.

Specific underlying molecular events may also be captured during radiomic analysis and there is a known association between MRI conspicuity and underlying biological events at the genomic level [9]. Previous work has suggested potential value in the longitudinal evaluation of quantitative parameters extracted from MR images (e.g., the Apparent Diffusion Coefficient–ADC–from diffusion-weighted imaging) [10]. Changes in prostate cancer volume on MRI imaging similarly provides an objective measure of response to treatment or disease progression. Volume measures are used during standard of care surveillance and form a key component of the clinical Prostate Cancer Radiological Estimation of Change in Sequential Evaluation (PRECISE) score which estimates the likelihood of radiological progression in patients on active surveillance for prostate cancer with serial mpMRI [11]. Emerging imaging techniques such as hyperpolarised MRI use carbon-13 enriched metabolites as tracers, in particular 13C-pyruvate, to capture the metabolic activity of tumours and may dramatically improve the sensitivity for detection of aggressive tumours when used alongside traditional mpMRI imaging [12]. mpMRI texture analysis has also shown promise in detection and risk stratification of MR-visible cancers [13]. RECONCILE will provide a platform for each of these imaging techniques to be further evaluated.

#### 1.2 Aims and objectives

RECONCILE (NCT04340245) will identify molecular and radiomic markers associated with clinical, pathological and radiological change in a cohort of localised MRI visible Gleason 3 + 4 tumours (n = 60). Markers will be correlated against diagnostic MRI-targeted histology and oncological outcomes.

The primary objective is to estimate the association of molecular changes with radiological progression (i.e., PRECISE 4 and 5) events of small, localised Gleason 3 + 4 cancer visible on MRI. Secondary and exploratory objectives include opportunity for further analysis of clinical and radiological progression events within the cohort, emerging imaging techniques (radiomic analysis and hyperpolarised MRI sequencing), identification of molecular mechanisms underlying cancer progression events, exploration of localised prostate cancer immune contexture and tumour micro environement and evaluation of participant quality of life scores using validated questionnaires. RECONCILE will provide an opportunity to derive models for prediction of prostate cancer progression risk based on molecular, imaging and histological analysis.

## 2. Design and methods: The RECONCILE study protocol

### 2.1 Study overview

RECONCILE is a single-centre, prospective, longitudinal, observational cohort study of patients recently diagnosed with localised prostate cancer. The study represents level 1b evidence for prognostic and diagnostic studies [14]. This manuscript is based upon study protocol version 2.0 10July2020.

RECONCILE will recruit 60 evaluable participants with a PSA of ≤ 15ng/ml, organ-confined Gleason 3 + 4 cancer (MCCL ≤ 10mm) and an MR concordant lesion (Likert or Prostate Imaging Reporting and Data System—PI-RADS—4 or 5) who have chosen to pursue active surveillance. Participants must have no history of prior prostate cancer treatment or anti-androgen exposure in the preceding 6 months (including 5-alpha reductase inhibitors) to be eligible for enrolment. Full inclusion and exclusion criteria are outlined in Table 1.

**Table 1 pone.0295994.t001:** RECONCILE study inclusion and exclusion criteria.

**Inclusion Criteria**
Adult aged 18 years or above
Diagnosed with prostate cancer Overall Gleason score 7 (3+4) within 12 months of entry
Likert or PIRADS score greater than or equal to 4
PSA less than or equal to 15 ng/ml in the last 6 months
Multiparametric MRI concordant with histology
Maximum cancer core length less than or equal to 10mm
Patients on active surveillance
**Exclusion Criteria**
Any contraindication to MRI scans (e.g. metal implants, unmanageable claustrophobia)
Radiological progression on any pre-enrolment MRI prostate following a previous histological diagnosis of Gleason 7 (3+4) prostate cancer
Presence of a pacemaker
Presence of a hip replacement
Any hormonal treatment or inhibitors of 5 alpha-reductase in the previous 6 months
Any previous TURP or other prostate surgery
Previous treatment for prostate cancer
Patients who have previously had sepsis due to a prostate biopsy
Patients receiving concomitant treatment for their cancer
Inability to provide full informed consent (e.g. due to dementia)

Tumour and fluidic samples will be subject to molecular analysis at baseline and one year. All participants will donate blood, urine and prostate tissue at baseline and one year. Prostate tissue will be collected during targeted transperineal prostate biopsy, directed to the MRI lesion of interest. A small subset of participants who are also enrolled in the Prostate Liquid Study (PLiS) (NCT04102904) will be invited to donate an interval semen sample at one year. A baseline semen sample will be shared from PLiS with the patients’ consent. For continuity, multiparametric MRI will be acquired on the same scanner (either 1.5T or 3T / only 3T) at baseline and interval. Radiomic features from standard of care multiparametric MRI will be extrapolated at baseline and one year. Molecular and radiomic markers of disease, and disease progression, will be identified during the final multivariate analysis.

Participants exit the study after 12 months and revert to the NHS standard of care prostate cancer pathway. No further study visits are required. Long-term participant follow-up through national healthcare records will then commence. Longitudinal outcomes (time to metastasis and disease-specific death) will be informed by long-term healthcare data linkage via national health records.

Participants who are also enrolled to the VALIDATE-PRO Study (NCT05017181) will have the opportunity to share data from their baseline and interval VERDICT, Luminal Imaging and hyperpolarised MRI studies for further analysis within RECONCILE [15–17]. The SPIRIT schedule of enrolment, interventions and assessments summarises study design (Fig 1).

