**Fig 2 pone.0295994.g002:**
[figure not shown]
A & B: RECONCILE participant pathway.

Participants recruited following participation in ReIMAGINE Risk will consent to the sharing of their biological samples and MR imaging with RECONCILE. Therefore, no additional baseline interventions are required for those recruited to RECONCILE from ReIMAGINE. Participants will, however, consent to donation of tissue and MRI data at one year.

An alternative route of entry is at the time of standard of care confirmatory targeted biopsy. This will normally follow a specialist referral to our centre for disease re-stratification and/or management. Such patients must have been diagnosed with Gleason 3 + 4 prostate cancer within 12 months of entry to RECONCILE and meet all other eligibility criteria. Research samples (blood, urine and prostate tissue) will be collected at the time of standard of care confirmatory targeted prostate biopsy. A repeat mpMRI prostate is also required as per local NHS protocol, a copy of which will be used for research. Interval research samples will be collected at one year.

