**Fig 3 pone.0295994.g003:**
[figure not shown]
Schedule of RECONCILE study visits.

*Visit 1 (baseline)*

The baseline visit consists of two encounters: a standard of care MRI prostate and a subsequent tissue donation visit at the time of standard of care NHS prostate biopsy. At the biopsy encounter, research blood, urine and prostate tissue will be collected.

Research data including baseline medical history and patient reported outcome (PRO) questionnaires will be collected on or before the standard of care biopsy visit. Baseline medical history review may take place over the telephone.

Participants enrolling to RECONCILE following participation in the ReIMAGINE Risk or PLiS studies will not be required to donate research blood, urine or prostate tissue at baseline. Instead they will consent to data and sample sharing from ReIMAGINE Risk or PLiS to RECONCILE.

*Follow-up PSA visits (3, 6 and 9 months)*

Following the baseline visit, clinical results will be provided in a standard of care NHS prostate cancer clinic. If active surveillance remains a suitable management option, the participant will proceed to interval 3 monthly PSA testing and clinic review as per national guidance. PSA kinetic data will be collected prospectively for research and entered into the study database.

*Interval (exit) visit (12 months)*

Interval (exit) investigations will take place 12 months after baseline tissue collection and consists of two standard of care encounters: an MRI prostate visit and subsequent targeted transperineal prostate biopsy. Again, research blood, urine and prostate tissue will be collected during the standard of care biopsy visit. PRO questionnaires will be posted to participants ahead of the biopsy visit and can be returned to study staff either by post or in person. Participants enrolled in the PLiS study will be invited to donate a semen sample at the time of study completion. This will be collected at home and returned to the study laboratory by post.

*Suspected progression*

Interval investigations, and exit from the study, may occur prior to the 12-month mark if there is suspicion of progression during PSA follow up. As is usual practice, standard of care mpMRI will be expedited and exit research samples collected (PROs, blood, urine, prostate tissue +/- semen) should the patient proceed to standard of care prostate biopsy.

*Non-visit*

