### 7.2 Secondary outcomes

Secondary objectives span imaging, pathology, molecular and clinical features and include:

*Imaging*

Time to radiological progression on standard of care MRI scan (i.e. evidence of MRI change either at planned standard of care MRI scan at one year from baseline, or on an expedited standard of care prior to thisQuantitative and qualitative assessment of MRI lesion(s) imaging characteristicsQuantitative imaging features (MRI and derivative) of the MRI lesion(s), a radiological progression ring (region of interest of the periphery within the MRI lesion at follow up which did not harbour abnormal signal at baseline), if present, and the rest of the prostate at different time pointsQualitative imaging features (MRI and derivative) of MRI lesion(s), a radiological progression ring (if present) and the rest of the prostate at different time pointsQuantitative imaging characteristics of MRI lesion(s), a radiological progression ring (if present) and the rest of the prostate at different time points and stratification according to radiological progression vs non progression

*Histology*

Qualitative and quantitative histologic composition of cancer lesions and their surrounding tissueHistological heterogeneity of cancer, both qualitatively and quantitatively

*Molecular analysis*

The molecular index (as defined in section 4.4.1 of this protocol) of the cancer lesion in question, as well as the surrounding peritumoral and normal tissueQualitative and quantitative analysis of urinary and seminal biomarkersQualitative and quantitative analysis of inflammatory infiltrate in the cancer lesion, peritumoral and normal tissueAnalysis of blood-based biomarkers related to immune surveillance and inflammatory cytokinesQualitative and quantitative analysis of immune related pathways

*Clinical data*

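### The radiological-progression exclusion runs to enrolment, but for men from ReIMAGINE the observation window opens earlier, so the same MRI finding can be an exclusion before consent and an outcome after it

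*Protocol article*

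**What the plan says.** All places are in the protocol article.

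- **Exclusion (Table 1).** "Radiological progression on any pre-enrolment MRI prostate following a previous histological diagnosis of Gleason 7 (3+4) prostate cancer". The rule is not limited to one entry route, and Section 2.1 presents Table 1 as the full set of criteria.
- **Entry limit (Table 1).** "Diagnosed with prostate cancer Overall Gleason score 7 (3+4) within 12 months of entry".
- **ReIMAGINE route (Section 4.1, text under Fig 2).** "Participants recruited following participation in ReIMAGINE Risk will consent to the sharing of their biological samples and MR imaging with RECONCILE", so that "no additional baseline interventions are required for those recruited to RECONCILE from ReIMAGINE". Section 5.2 adds that these men "will not be required to donate research blood, urine or prostate tissue at baseline".
- **Tertiary route (Section 4.1).** Research samples are taken at the confirmatory biopsy, and a repeat mpMRI is required.
- **Clock (Section 5.2).** "Interval (exit) investigations will take place 12 months after baseline tissue collection".
- **Early events (Section 5.2).** "Interval investigations, and exit from the study, may occur prior to the 12-month mark if there is suspicion of progression during PSA follow up".
- **Time to progression (Section 7.2).** This counts "evidence of MRI change either at planned standard of care MRI scan at one year from baseline", or change on an expedited scan before then.
- **Primary outcome (Section 7.1).** The proportion of concordant molecular and radiological pairs at exit.

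**The concern.** Eligibility and follow-up use different starting points. In the tertiary route, baseline tissue is taken at study entry, so an exclusion that runs to enrolment removes only men who had progressed before observation began. In the ReIMAGINE route, observation starts at tissue already in store and enrolment comes later. Any MRI in between falls inside the study's own window. If it shows progression, the man cannot enter; if it shows stability, he can.

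This is selection on the outcome, or equivalently an event-free period required before entry, in one route only. The men at risk of being lost are early progressors, while Section 3 states that the study is about the first identifiable progression event. The quantities at stake are the radiological progression rate, time to progression, the proportion of concordant pairs, and the comparability of the two routes.

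The two 6-month windows in Table 1 (PSA, and hormonal treatment or 5-alpha-reductase inhibitors) raise a related anchoring question. Section 2.1 ties the drug window to eligibility for enrolment, so it does not by itself describe the 6 months before tissue that was taken earlier in ReIMAGINE.

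**Working it through.** **1. The plan's own figure.** The article gives no number for this point. The nearest is the power in Section 8: N = 60, two-sided alpha 0.05, discordant proportions 0.05 and 0.25, power at least 0.8. With s = 0.05 + 0.25 = 0.30 and d = 0.25 − 0.05 = 0.20, the Miettinen formula is

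n = [1.96·s + 0.8416·√(s² − d²(3+s)/4)]² / (s·d²) = [0.588 + 0.8416·√0.057]² / 0.012 = 51.9, so 52.

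At N = 60 the power is 0.862. The stated figure holds and is not in dispute.

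**2. The dates side by side.**

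| | Tertiary route | ReIMAGINE route |
|---|---|---|
| Baseline tissue and MRI | at study entry | already taken in ReIMAGINE |
| 12-month clock starts | baseline tissue | baseline tissue |
| Exclusion ends | enrolment | enrolment |
| Exclusion overlaps the window | no | yes, from tissue to consent |

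For a man who consents g months after baseline tissue, the overlap is g/12 of his window: 25% at 3 months, 50% at 6, 75% at 9. The only limit stated is 12 months from diagnosis. This takes the ReIMAGINE biopsy to be the diagnostic one, which the article implies but does not state.

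**3. Illustrative loss within the ReIMAGINE route.** None of these inputs is in the article. Assume that 20% of men progress by 12 months, that a share e of them is seen on an expedited MRI spread evenly over the year, and that the gap is L months. Then

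share of progressors lost = e·L/12; observed rate = 0.20(1 − lost)/(1 − 0.20·lost).

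| e | L | Lost | Observed rate |
|---|---|---|---|
| 25% | 2 | 4.2% | 0.1917/0.9917 = 19.3% |
| 25% | 6 | 12.5% | 0.175/0.975 = 17.9% |
| 50% | 6 | 25% | 0.15/0.95 = 15.8% |
| 50% | 12 | 50% | 0.10/0.90 = 11.1% |

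The last row is a boundary case, because consent would coincide with the exit visit. Even spacing probably overstates short gaps, since the first scheduled PSA after baseline is at 3 months.

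**4. Effect on the 2×2 table.** Let f be the share of all progressors lost across the whole cohort (route share times loss within the route). Multiply the R+M+ and R+M− cells by (1 − f), rescale to 1 and recruit back to 60. Section 8 does not say which discordant cell is 5% and which is 25%, so both are shown, with R+M+ assumed to be 0.10. Concordance is R+M+ plus R−M−.

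| | f = 0 | 0.1 | 0.3 | 0.5 |
|---|---|---|---|---|
| **R+M− 0.25, R−M+ 0.05** | | | | |
| R+ | 35% | 32.6% | 27.4% | 21.2% |
| Concordance | 0.700 | 0.715 | 0.749 | 0.788 |
| Power | 0.862 | 0.794 | 0.590 | 0.320 |
| **R+M− 0.05, R−M+ 0.25** | | | | |
| R+ | 15% | 13.7% | 11.0% | 8.1% |
| Concordance | 0.700 | 0.701 | 0.702 | 0.703 |
| Power | 0.862 | 0.898 | 0.955 | 0.987 |

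Example, first block, f = 0.1: concordance = (0.09 + 0.60)/(1 − 0.1 × 0.35) = 0.69/0.965 = 0.715. With R+M+ = 0.20 in the second block, concordance falls instead, from 0.700 to 0.697 at f = 0.1 and 0.686 at f = 0.5.

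**5. Association.** If loss depends on R+ alone, the odds ratio does not change, because (1 − f) cancels: 0.10 × 0.60/(0.25 × 0.05) = 4.8 at every f, in both blocks.

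**The case against.** The strongest reply is that the rule suits the tertiary route, where men arrive with an earlier diagnosis and have a repeat MRI, and that it rarely operates in the other route. ReIMAGINE runs at the same site, its logs are screened weekly, and all eligible men are offered enrolment (Section 5.1). Follow-up PSA data are collected prospectively, which fits early consent. The planned MRI is at 12 months, so a scan in the gap would usually be one expedited on suspicion. A cap on the gap may also sit in the full protocol or in the figures, which are not shown.

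Most of this stands as to size. It does not change the rule: the criterion is written for every route, and nothing in the article caps the gap below 12 months or ties the exclusion to baseline. Section 4.8 does not settle the matter either. It reports 62 recruited and 37 with donated baseline samples, but the other 25 could be men who consented before biopsy or men whose ReIMAGINE samples are shared.

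A reader might infer that progressors are in fact being screened out, or that the molecular-radiological association is biased towards the null. The article supports neither. The first needs a gap and an MRI within it, and no instance is documented. The second needs the lost progressors to differ molecularly from the retained ones; loss on R+ alone leaves the odds ratio intact.

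A reader might also count the active-surveillance criterion as a second filter of this kind. That criterion defines the target population. Whether the drug window matters in practice depends on ReIMAGINE's own eligibility rules, which are not shown.

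**Conclusion.** The point holds as a flaw in the anchoring of an eligibility rule. For ReIMAGINE entrants, the period in which progression excludes a man overlaps the period in which progression is the outcome. Entry by this route can therefore be conditioned on the radiological half of the primary outcome. The tertiary route is not affected.

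The size cannot be computed from the article. On the assumptions above it runs from negligible (19.3% observed against 20% with a two-month gap) to material (15.8% with a six-month gap and half of progressors scanned early), before scaling down to the ReIMAGINE share of the cohort. The radiological progression rate, time to progression and concordant proportion are shifted. Power can move either way, and no direction is established for the association. The stated sample size and power are unaffected if no progressor is lost in the gap.

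The correction is worth making because it is cheap and because analysis cannot recover men who were never enrolled.

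**What to change.** 1. Reword the Table 1 exclusion, for both routes, as radiological progression on any MRI after the 3+4 diagnosis and before baseline tissue collection. This runs up to and includes the baseline MRI, so a tertiary man's repeat MRI is still covered. Ending the rule before the baseline MRI would leave that scan out. Admitting only men with no MRI since baseline, whatever its result, would still drop early progressors.
2. Treat a progression MRI after baseline tissue as a study outcome where exit samples can still be collected.
3. Date the two 6-month windows (PSA; hormonal treatment or 5-alpha-reductase inhibitors) to baseline tissue collection, leaving their length as it is.
4. For men already enrolled, record the interval from tissue to consent and any MRI within it. Report from the screening log how many candidates were excluded for progression in that interval.
5. Repeat the primary analysis without men who had an MRI in the interval.

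The cost is a wording amendment, two date fields and one sensitivity analysis. The sensitivity analysis shows how far the result depends on the gap; it does not restore men never enrolled, so the rewording matters more. Section 4.8 reports only 5 men with completed follow-up and replacements still being recruited, so at the time of writing the change could still apply to later entrants.

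### For men entering from ReIMAGINE, the 6-month drug exclusion is counted back from enrolment, not from the earlier baseline scan and biopsy, so it can miss exposure at baseline.

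*Protocol article*

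**What the plan says.** The exclusion list in Table 1 bars "Any hormonal treatment or inhibitors of 5 alpha-reductase in the previous 6 months" and names no reference date. Section 2.1 supplies one: participants must have had no "anti-androgen exposure in the preceding 6 months (including 5-alpha reductase inhibitors) to be eligible for enrolment". As written, the window is counted back from enrolment.

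Section 4.1 (text with Fig 2) describes two ways in. Men who come from ReIMAGINE share the samples and MR images they already gave, so "no additional baseline interventions are required for those recruited to RECONCILE from ReIMAGINE". For the rest, "An alternative route of entry is at the time of standard of care confirmatory targeted biopsy", and their research samples are taken at that biopsy.

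Two other timings matter. Table 1 requires a man to be "Diagnosed with prostate cancer Overall Gleason score 7 (3+4) within 12 months of entry". Section 5.2 states that "Interval (exit) investigations will take place 12 months after baseline tissue collection", so the exit date follows the baseline tissue and not enrolment.

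Table 1 also excludes "Previous treatment for prostate cancer" with no time limit and, in a separate line, men under current treatment for the cancer.

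**The concern.** The primary analysis compares each man with himself. Molecular progression (section 4.4.1) is a difference between baseline and follow-up indices above a threshold. Radiological progression (section 4.5) is PRECISE 4 or 5 on serial MRI. Neither definition has a term for drug exposure. Blinding (sections 4.3, 4.4.1 and 4.6) keeps one assessment from influencing the other, but it cannot remove an exposure that was present at one time point and absent at the other.

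An exclusion window protects such a comparison only if it covers the baseline measurement. On the ReIMAGINE route the window is attached to a later date. If a man's baseline pair was obtained on an androgen-acting drug and his exit pair off it, a change in molecular index or PRECISE score could reflect withdrawal of the drug and not the tumour.

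**Working it through.** **Inputs.** Look-back of 6 months from enrolment (Table 1 and section 2.1). Diagnosis at most 12 months before entry (Table 1). ReIMAGINE baseline collected before entry (section 4.1). Exit 12 months after baseline tissue (section 5.2). N = 60, discordant proportions 0.05 and 0.25, two-sided 0.05, McNemar's test with the Miettinen approximation (section 8).

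**Step 1: the plan's own power figure.** With ψ = 0.05 + 0.25 = 0.30 and d = 0.25 − 0.05 = 0.20:

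power = Φ{[√(nψ)·d − 1.96ψ] / √[ψ² − d²(3 + ψ)/4]}

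= Φ{[√18 × 0.20 − 0.588] / √(0.09 − 0.033)} = Φ(0.2605 / 0.2387) = Φ(1.09) = 0.862.

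The statement of at least 0.8 is reproduced, and the sample size is not in question here.

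**Step 2: does the window reach baseline?** Let G be the months from baseline tissue to enrolment on the ReIMAGINE route. Assumption: baseline tissue is the diagnostic biopsy, so G lies between 0 and 12.

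- Part of the 6 months before baseline that is covered = max(0, 6 − G).
- Time by which the baseline date falls outside the window = max(0, G − 6).
- Look-back from enrolment needed to cover the same 6 months before baseline = G + 6.
- Time from enrolment to exit = 12 − G.

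| G (months) | Pre-baseline months covered | Baseline outside window by | Look-back needed | Enrolment to exit |
|---|---|---|---|---|
| 0 | 6 | 0 | 6 | 12 |
| 3 | 3 | 0 | 9 | 9 |
| 6 | 0 | 0 | 12 | 6 |
| 9 | 0 | 3 | 15 | 3 |
| 12 | 0 | 6 | 18 | 0 |

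For any G above 0, part of the pre-baseline period is missed. For G above 6, the baseline date itself is missed. A man on the drug at baseline who stopped within the first G − 6 months afterwards passes the rule: within 3 months at G = 9, within 6 months at G = 12. On the referral route G is about 0 and the first row applies.

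**Step 3: what an exposed man could do to the test.** McNemar's statistic uses only the discordant cells. With the planning proportions these hold 60 × 0.05 = 3 and 60 × 0.25 = 15 men, so the statistic is (15 − 3)²/(15 + 3) = 8.0.

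- One man moved between the two concordant cells: still 8.0, and total concordance stays at 42 of 60.
- One man moved from a concordant cell into the smaller discordant cell: (15 − 4)²/19 = 6.37.
- One man moved into the larger discordant cell: (16 − 3)²/19 = 8.89.

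The Step 1 formula shows the same pattern for power. The shares moved are assumptions, since the article gives no exposure rate.

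| Share moved (men of 60) | Power if moved to smaller cell | Power if moved to larger cell |
|---|---|---|
| 2% (1.2) | 0.72 | 0.91 |
| 5% (3) | 0.50 | 0.96 |
| 10% (6) | 0.22 | 0.99 |

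**The case against.** The strongest reply is that few men, perhaps none, will meet the conditions. A man must have been on the drug at his ReIMAGINE biopsy, must have stopped soon afterwards, and must have enrolled more than 6 months later. ReIMAGINE's own eligibility criteria are not in the article and may already bar such men. Section 5.1 has its recruitment logs screened weekly, and section 5.2 collects PSA prospectively at 3, 6 and 9 months after the baseline visit. Both point to enrolment soon after diagnosis. This stands as an argument about frequency. It does not close the gap, because Table 1 allows entry up to 12 months after diagnosis.

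It is also fair that no passage states what these drugs do to expression profiles or MRI appearance, or why the exclusion exists. An effect on either axis is plausible but not documented.

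Three stronger readings are tempting and should not be drawn.

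- **That the gap affects the whole cohort or all hormone treatment.** Referral entrants give baseline tissue at entry, and the two treatment exclusions in Table 1 already remove cancer-directed hormones.
- **That men who start such a drug after entry remain evaluable.** Any eligibility criterion stops at entry, and a follow-up rule may sit in the full protocol. Section 4.8 refers to non-evaluable cases without defining them, and nothing says these men are kept.
- **That drug withdrawal inflates the primary result through false joint progression.** Under independence, the planning proportions give cells of 1.1, 3, 15 and 40.9. Moving one man from joint non-progression to joint progression raises the odds ratio from 1.0 to (2.1 × 39.9)/(3 × 15) = 1.86. But section 8 plans McNemar's test, not an odds ratio, and Step 3 shows that this move leaves the test and total concordance unchanged. Only if section 7.1 is read as counting joint progressors alone would the primary proportion move, and the article does not settle that reading. With a starting cell of 1.1, any one man would nearly double the ratio.

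**Conclusion.** The concern holds for the ReIMAGINE route only. The exclusion in Table 1 and section 2.1 is anchored to a date that can fall up to about 12 months after the baseline measurement it ought to cover. Once the gap exceeds 6 months, a man exposed at baseline can be eligible, with withdrawal falling between the two compared time points. The drugs concerned are 5-alpha-reductase inhibitors and hormonal drugs given for other reasons.

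The 12-month figure assumes that the baseline tissue is the diagnostic biopsy. The size and direction of any bias cannot be derived from the article: it gives no exposure rate, effect size or distribution of the gap. The power figures in the working show only that a handful of men could matter in either direction if they moved into a discordant cell. The length of the look-back is not challenged here, only the date from which it is counted.

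**What to change.** Reconcile Table 1 and section 2.1 with section 4.1 by counting the same look-back from the baseline MRI and the baseline research biopsy, whichever study collected them. On the referral route this changes almost nothing.

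Section 4.8 reports 62 men already recruited, so rewording alone reaches only later entrants and replacements. For men already enrolled by the ReIMAGINE route, check the start and stop dates of these drugs in existing records. Then report the primary contingency table with and without any man exposed at baseline.

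The cost is one reworded criterion, a records check and one sensitivity table. The downside is that a few ReIMAGINE entrants may be screened out, or may appear only in the sensitivity table. Clinical care is not affected.
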